### Data management

All source data will be kept confidential in secured locations with restricted access by authorised personnel only inclusive of monitors, auditors and reviewers of ethical and regulatory committees in line with applicable data privacy regulations. Each participant is asked to consent to this handling of the data and is assigned a pseudonymous identification number that is used throughout the study on all source data.

Accurate documentation of paper-based and electronic source data, for example, original records and certified copies of original records, progress notes, screening logs and recorded data from automated instruments, will be maintained. The pseudonymised clinical data captured on paper-based Case Report Forms will be entered at the sites into a database using the web-based Clinical Data Management System of OpenClinica (OpenClinica LLC, Waltham, Massachusetts). The study-specific database has been built, maintained and hosted by the LMU Klinikum on a centralised secure server. Data modifications and necessary corrections performed in the database also within the context of double data entry will be documented and tracked in audit trails. Data quality and plausibility are assured by a series of preprogrammed edit and range checks in OpenClinica. Further validation checks are programmed in Stata (Statacorp, College Station, Texas) with extracts of the database and electronically received data, for example, spirometry, dCXR and laboratory, will be integrated into analyses of datasets.

### Monitoring

Assigned study monitors will visit the sites at regular intervals physically and/or virtually in addition to frequent day-to-day communication. Close follow-up on all study-related aspects will be performed to ascertain compliance with standards of Good Clinical Practice, the Declaration of Helsinki and other local and national regulatory guidelines inclusive of guidelines for infection prevention and control of airborne-transmitted diseases, for example, social distancing in well-ventilated spaces, and wearing of personal protective equipment. In particular, monitors that support designated study personnel are responsible to verify (1) adequacy of the study personnels’ qualifications and facilities, (2) accuracy of informed consent procedures and patient eligibility, (3) adherence to the study protocol, (4) protection of rights and well-being of participants, (5) adherence to infection prevention and control measures, (6) accuracy and completeness of study documents and other study-related records and (7) maintenance of source documents.

### Ethics and dissemination

The study protocol and informed consent/assent documents have been approved by regulatory and ethical committees of the participating institutions (Medical Research Council in Zimbabwe (MRCZ/A/2618), the National Health Research Ethics Committee in Tanzania (TMDA-WEB0021/CTR/0004/03), the National Bioethics Committee for Health in Mozambique (541/CNBS/21), and the ethical committees of London School of Hygiene & Tropical Medicine, United Kingdom (22 522–2) and the medical faculty of the Ludwig-Maximilians-Universität München, Germany (20–0771)).

Adult ICs and HHCs are asked for written informed consent prior to their participation. Underage HHCs are asked for assent in addition to obtaining the consent of their legal guardians/parents; with ages for assent depending on local guidance. In case of illiteracy, the participant is asked to give its consent by fingerprint while an adult impartial, literate witness present during the entire consent procedure signs the consent on behalf. All participants have the right to withdraw from the study at any time. Findings derived from ERASE-TB will be presented at scientific conferences and published in peer-reviewed international journals.

### Current study status

The recruitment of ICs and HHCs is in progress in Zimbabwe, Mozambique and Tanzania since March, August and September 2021, respectively. The follow-up of HHCs is anticipated to be completed in March, August and September 2023 in Zimbabwe, Mozambique and Tanzania, respectively; laboratory analyses are estimated to be performed by December 2024.

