**Methods and analysis:**

A total of 2100 HHCs (aged ≥10 years) of adults with microbiologically-confirmed pulmonary TB will be recruited and followed up at 6-month intervals for 18–24 months. At each time point, a WHO symptom screen and digital chest radiograph (dCXR) will be performed, and blood and urine samples will be collected. Individuals screening positive (WHO symptom screen or dCXR) will be requested to provide sputum for Xpert MTB/Rif Ultra. At baseline, HHCs will also be screened for HIV, diabetes (HbA1c), chronic lung disease (spirometry), hypertension and anaemia. Study outcomes will be coprevalent TB (diagnosed at enrolment), incident TB (diagnosed during follow-up) or no TB at completion of follow-up. Novel diagnostics will be validated using fresh and biobanked samples with a nested case–control design. Cases are defined as HHCs diagnosed with TB (for early diagnosis) or with incident TB (for prediction of progression) and will be matched by age, sex and country to HHCs who remain healthy (controls). Statistical analyses will include assessment of diagnostic accuracy by constructing receiver operating curves and calculation of sensitivity and specificity.

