### Recruitment sites

Recruitment of ICs and HHCs at selected primary healthcare facilities and communities has commenced in Harare, Zimbabwe in March 2021, Maputo, Mozambique in August 2021, and Mbeya, Tanzania in September 2021. Partners of the ERASE-TB consortium are illustrated in figure 1. All three countries have a high TB incidence ranging from 100 to 499/100 000 population^1^ and HIV prevalence among adults aged 15 years and older of 5%–20%.^7^ The African research institutions have established collaborations with their respective National Tuberculosis Programs ensuring referral and appropriate follow-up of patients with TB. Figure 2 illustrates the geographic location of research institutions, healthcare facilities where recruitment is taking place, demographic characteristics of study populations and estimates on TB incidence and HIV prevalence.^8–15^

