### Study design

ERASE-TB is a non-interventional, longitudinal, prospective cohort study among HHCs aged ≥10 years exposed to highly infectious pulmonary TB ICs aged ≥18 years. Eligibility criteria are detailed in figure 3 and the study design is shown in figure 4. TB ICs are eligible if the bacterial load in their sputum is at least at the ‘medium’ level according to Xpert MTB/RIF or Xpert MTB/RIF Ultra, and they have received less than seven daily doses of anti-TB treatment before enrolment. This maximises the likelihood of culturing and storing *Mtb* isolates. The total study duration will be 36 months. This includes 12-month enrolment of ICs and HHCs, and 18-month to 24-month follow-ups of HHCs. Follow-up ends when a HHCs withdraws from the study, is lost to follow-up, dies or is diagnosed with TB and referred for treatment. Scheduled or unscheduled unwell visits can be conducted physically and/or telephonically in case of abnormal finding, for example, by abnormal digital chest radiograph (dCXR), or when a participant feels unwell in between scheduled follow-up visits.

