**Figure 3 F3:**
[figure not shown]
Eligibility criteria and schedules of events for index cases and household contacts. A=depending on the time point of study enrolment and consequently on the duration available for follow-up, that is, 18 or 24 months, the follow-up visit at 24 months±30 days may be conditional; B=the follow-up visit by phone may be conducted after the last scheduled follow-up visit at 18 months±30 days or 24 months ±30 days to assess whether symptoms suggestive of TB have occurred, TB diagnosis has been made or anti-TB treatment has been initiated; C=unwell visits by phone or on-site may be conducted between scheduled follow-up visits if a participant presents at a recruitment healthcare facility with signs and symptoms suggestive of TB; D=coached spontaneous or induced sputum collection for storage at scheduled follow-up visit at 18 months±30 days or 24 months ±30 days, and for repetition of HIV testing if tested negative at baseline; E=coached spontaneous or induced sputum collection on the decision of the investigating team for testing by Xpert MTB/RIF Ultra if participant presents with signs and symptoms suggestive of TB; F=coached spontaneous or induced sputum collection in case of Xpert MTB/RIF Ultra positivity or strong clinical suspicion of TB for repetition of the Xpert MTB/RIF Ultra; G=in case of HIV positivity to be followed by the assessment of CD4 counts; H=CXR to be conducted at an unscheduled on-site unwell visit on the decision of the investigating team depending on the nature of symptoms reported, and the time elapsed since the last CXR including its findings; I=not to be conducted among pregnant women; J=stored venous blood includes 6 mL EDTA blood for whole blood and plasma, 4 mL serum and 2.5 mL PAXgene blood, all samples will be deep frozen for retrospective testing using new diagnostics as described in text; K=in case the evaluation of symptoms of a participant unable to present at a recruitment healthcare facility is required an unscheduled on-site or home visit will be arranged by phone, the resolution of symptoms can alternatively be addressed by phone; L=collection of PBMC at baseline and follow-up visit at 6 months±30 days is optional, thus will not be performed at each participating site and for each participant; M=in case the evaluation of symptoms of a participant unable to present at a recruitment healthcare facility is required or doubtful if required an unscheduled unwell visit by phone will be arranged, the resolution of symptoms can alternatively be addressed by phone; N=spirometry and/or diabetes (HbA1c) will be performed at scheduled follow-up visits at 6 months±30 days, 12 months ±30 days and 18 or 24 months±30 days if required or not performed at baseline, anaemia (Hb) will be performed at baseline and scheduled follow-up visits at 6 months±30 days, 12 months ±30 days and 18 or 24 months±30 days if possible; O=blood pressure measurement will be performed at baseline and scheduled follow-up visits at 6 months±30 days, 12 months ±30 days and 18 or 24 months±30 days; P=WGS to be performed once *Mtb* infection is confirmed and an isolate could be recovered. CD4, cluster of differentiation 4; CXR, chest radiograph; Hb, haemoglobin; HbA1c, glycated haemoglobin; IGRA, interferon gamma release assay; LAM, lioparabinomannan; MTB, *Mycobacterium tuberculosis*; MBLA, molecular bacterial load assay; PBMC, peripheral blood mononuclear cell; RIF, rifampicin; TAM-TB, T- cell activation marker tuberculosis; TB, tuberculosis; WGS, whole genome sequencing.

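### The anticipated follow-up completion dates fall 24 months after each site's first recruitment and cannot fit 12 months of enrolment with 18 to 24 months of follow-up

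*Protocol article*

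**What the plan says.** The start dates are given twice and agree. Recruitment sites says that recruitment "has commenced in Harare, Zimbabwe in March 2021, Maputo, Mozambique in August 2021, and Mbeya, Tanzania in September 2021", and Current study status says that it "is in progress in Zimbabwe, Mozambique and Tanzania since March, August and September 2021, respectively". The same status section adds that follow-up of contacts "is anticipated to be completed in March, August and September 2023 in Zimbabwe, Mozambique and Tanzania, respectively", with laboratory work finished by December 2024.

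The design is set out under Study design: "The total study duration will be 36 months", and "This includes 12-month enrolment of ICs and HHCs, and 18-month to 24-month follow-ups of HHCs". The abstract repeats that contacts "will be recruited and followed up at 6-month intervals for 18–24 months", and the secondary objectives use the same range. Note A to Figure 3 allows for differing enrolment dates but offers only two lengths: "18 or 24 months, the follow-up visit at 24 months±30 days may be conditional". Nothing in the article provides for less than 18 months in a contact who stays in the study without a TB diagnosis.

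**The concern.** The interval from first recruitment to the end of follow-up has to hold both the enrolment period and the follow-up of the last person enrolled. The printed dates leave 24 months for a design that needs at least 30.

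The end date sets how long the primary endpoint is observed. Incident TB is counted over follow-up, and controls are contacts who stay free of TB over the same period (Statistical analyses). The test evaluations also use stored samples at several intervals before diagnosis. If sites really closed on the printed dates, there would be fewer late visits, fewer samples taken long before diagnosis, and some controls classified on shorter observation than the design promises. The article's own list of limitations already says that the small number of TB cases limits power.

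**Working it through.** **Inputs.** Starts: March, August and September 2021 (Recruitment sites; Current study status). Ends: March, August and September 2023 (Current study status). Enrolment 12 months, follow-up 18 to 24 months, total 36 months (Study design). Visits ±30 days (Figure 3 legend), taken here as one month. Contacts: 700 per country, 2100 in all; 49 incident and 15 coprevalent cases (Sample size). Assumption: uniform enrolment.

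**The plan's own figures.** The 36 months reproduces as 12 + 24. The case counts agree: 49 + 15 = 64, and 64/2100 = 3.05%. Exact (Clopper-Pearson) intervals reproduce the printed ones: 36/49 gives 59–85%, 40/49 gives 68–91%, 180/196 gives 87–95% and 184/196 gives 90–97%.

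**Calendar check.** Longest follow-up = end − start. Shortest = end − (start + 12). Earliest end that gives everyone 18 months = start + 12 + 18.

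| Site | Start | Printed end | Longest | Shortest, 12 months per site | Earliest end for 18 months |
|---|---|---|---|---|---|
| Zimbabwe | Mar 2021 | Mar 2023 | 24 | 12 | Sep 2023 |
| Mozambique | Aug 2021 | Aug 2023 | 24 | 12 | Feb 2024 |
| Tanzania | Sep 2021 | Sep 2023 | 24 | 12 | Mar 2024 |

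The latest of these end dates, March 2024, is 36 months after the first site opened and before the December 2024 laboratory date.

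**Share short of 18 months, enrolment of 12 months per site.** A contact enrolled u months after opening has 24 − u months. This is below 18 when u > 6: 6/12 = 50%. With the visit allowed at month 17, it falls short when u > 7: 5/12 = 42%. Mean follow-up is 24 − 6 = 18.0 months. If sites ran to month 30, capped at 24 months per person, the mean would be ½ × 24 + ½ × 21 = 22.5.

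**Share short of 18 months, one common window, March 2021 to March 2022.** Minimum follow-up is 12 months in Zimbabwe, 17 in Mozambique and 18 in Tanzania.
- Below 18 months: Zimbabwe 700 × 6/12 = 350; Mozambique (7 months of enrolment, the last one short) 700 × 1/7 = 100; Tanzania 0. Total 450/2100 = 21%.
- Using the visit window: Zimbabwe 700 × 5/12 = 292; the others 0. Total 292/2100 = 14%.

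**Incident cases, illustration only, enrolment per site.** Sample size does not say what follow-up the 49 presumes.
- If it presumes a mean of 18 months: 49 × 18/18 = 49, no loss.
- If it presumes 22.5 months, by person-time: constant hazard 49 × 18/22.5 = 39; year-1 hazard three times that of year 2, 49 × (36 + 6)/(36 + 10.5) = 49 × 42/46.5 = 44.
- On the same premise, counting only to the last scheduled visit reached (ignoring the visit window): means of 15 versus 21 months, 49 × 15/21 = 35; with the 3:1 hazard, 49 × (36 + 3)/(36 + 9) = 49 × 39/45 = 42.
- If it presumes 24 months for everyone, constant hazard: 49 × 18/24 = 37.

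At 40 cases, 29/40 (72.5%) has an exact interval of 56–85%, against 59–85% for 36/49.

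**The case against.** The best reply is that the dates sit in a status section and are projections. The design text is consistent about 18 to 24 months, no section tells sites to stop 24 months after opening, and later dates would fit both the 36-month duration and the laboratory date. A dating slip is therefore plausible. That stands, and it makes every consequence conditional on sites really closing in 2023. It does not remove the contradiction, because a projection must still fit the design beside it.

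A second reply is that the 12 months may be one enrolment window for the whole study. Study design does not say which it is. This reading narrows the problem to 21%, or to Zimbabwe alone once the visit window is used, but Zimbabwe's minimum remains 12 months.

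A third is that sites may have enrolled faster. The 2023 dates would need each site to close within 6 months of opening, so Zimbabwe by September 2021. The article reports recruitment as in progress at all three sites, and Tanzania opened only in September 2021, so Zimbabwe was still recruiting in that month or later. No shorter window is stated.

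Three stronger readings are tempting but unsupported.
- A reader might infer that half the cohort must miss the 18-month visit. That needs a separate 12-month window per site and ignores the ±30 days.
- A reader might infer that half the controls would be called TB-free after only 12 months. On the per-site model, the short-follow-up contacts have 12 to 18 months. Unwell visits can occur in between, and note B to Figure 3 allows a closing phone call. The 196 controls are a matched selection, and nothing shows that half would come from this group.
- A reader might infer a definite loss of incident cases. The article never gives the follow-up length behind the 49, so no loss is also possible.

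**Conclusion.** The contradiction is certain to the month, the only precision the article gives: 24 months are printed where the design needs at least 30, and no reading removes the conflict for Zimbabwe. Assuming uniform enrolment, the share of contacts unable to reach month 18 is 42–50% if each site enrols for 12 months, and 14–21% if there is one common window from March 2021; the lower figure in each pair uses the visit window.

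The effect on precision is uncertain and looks modest. Under per-site enrolment and actual closure in 2023, incident cases range from the full 49 to roughly 35–44, depending on the follow-up assumed for the 49 and on how early progression occurs. At 40 cases, the lower limit for a sensitivity of about 73% moves by three percentage points. This is a wrong or unreconciled date that matters because it governs how long the primary endpoint is observed. It does not show that the planned case count will be missed.

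**What to change.** Reconcile Current study status with Study design, and state whether the 12-month enrolment applies per site or to the whole study. Then take one of two routes.

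- **Keep 18 to 24 months.** Restate completion as last contact enrolled plus 18 months. With per-site enrolment that is no earlier than September 2023 (Zimbabwe), February 2024 (Mozambique) and March 2024 (Tanzania). If 2023 was a slip, this costs one sentence. If sites had planned to close on the printed dates, it costs up to 6 further months of follow-up, inside the stated 36-month duration.
- **Keep the 2023 dates.** Change the range to 12 to 24 months wherever 18 to 24 appears (abstract, Study objectives, Study design and the Figure 3 notes). State the follow-up length behind the 49 incident and 64 total cases, and check whether those counts and the intervals in Sample size still hold. The cost is a possibly lower case count and slightly wider intervals.
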